### **2. Aims of the research**

1. To investigate the effects of long-term vegan and omnivorous diet on gut metagenomics in ultra-marathoners,
2. To determine the adaptation of the gut microbiome to extreme endurance exercise according to the vegan or omnivorous diet in ultra-marathoners,
3. To determine energy availability, macro, and micronutrient intakes before, during, and after the race and compare the differences between vegan and omnivorous ultra-marathoners.
4. To explore the effects of long-term vegan and omnivorous diets on exercise capacity, oxidant/antioxidant capacity, and muscle fatigue in ultra-marathoners

### **3. Preliminary data supporting the research**

With several elite athletes adopting veganism, a vegan diet has become more popular in the athletic population [1]. The vegan diet, which eliminates all animal products from an individual's diet, promotes health benefits that include a lower risk of cardiovascular disease, diabetes, obesity, hypertension, and cancer [2–4]. However, veganism has raised concerns about possible nutrient deficiencies, mainly protein, w-3, vitamin B12, zinc, and calcium [4,5]. Although the popularity of the vegan diet has increased among athletes, its effects on health and performance are still contentious. Additionally, there is a lack of research into the vegan dietary pattern in the athletic population [6].

According to a review by Pingitore et al. [7], while moderate exercise is defined as beneficial for endogenous antioxidant defenses, exhaustive/ long-duration performance could cause excessive release of stress hormones and products that alter the body redox balance. Therefore, although well-trained athletes might be resistant to increased reactive oxygen species (ROS), exhaustive exercise and inadequate recovery in the ultra-endurance athletes have been associated with the excessive production of lipid peroxidation and ROS, which alters body homeostasis and causes both cellular and tissue damage [8,9]. The excessive release of stress factors causes an increase of lipopolysaccharides (LPS) translocation outside of the gut, resulting in exercise-induced endotoxemia, thus increasing permeability [10]. While lipid peroxidation and ROS can be determined in the formation of metabolic products such as malondialdehyde (MDA) [11], reactive oxygen metabolites (d-ROMs) [12], the body's endogenous antioxidant capacity can be evaluated by measuring plasma total antioxidant capacity (TAC) [13], a whole measurement of both enzymatic and non-enzymatic antioxidants. Previous studies have reported that consuming fruits and vegetables rich in antioxidants instead of taking antioxidant supplementation is suggested as the best approach to maintaining the body's oxidative balance [14–16]. A vegan diet, rich in both antioxidants and flavonoids, which are naturally occurring anti-inflammatory factors [1], could be an effective strategy to regulate the microbiome, reduce muscle fatigue and improve performance in ultra-endurance athletes.

Muscle fatigue is a common phenomenon caused by an alteration in metabolic conditions that restricts life and has detrimental effects on exercise performance [17].

Detection of muscle fatigue-related biomarkers, thus developing potential strategies to reduce muscle fatigue, is crucial for managing the pathologic conditions and enhancing muscle endurance in athletes, particularly during exhaustive exercise [18]. The occurrence of muscle fatigue depends on several multifactorial conditions, including energy metabolism biomarkers such as lactate, hydrogen ions, and oxidative stress and inflammatory biomarkers such as plasma ROS, TAC, and tumor necrosis factor alpha (TNF- $\alpha$ ) [19]. Additionally, immunologic biomarkers such as heat shock proteins (HSPs) [20] and orosomucoid (ORM) [21] are classified as a novel strategy to modulate muscle fatigue and immuno-modulating activity. Accordingly, Wan et al. [19] has claimed that foods rich in vitamins, minerals, flavonoids, and w-3 fatty acids are promising dietary factors that may reduce muscle fatigue in athletic populations. More research is needed to determine the effects of vegan and omnivorous diets on exercise-induced muscle fatigue and immunological conditions in athletes.

As long-term, low-grade energy and both macro- and micronutrient deficiencies are common in ultra-endurance athletes, they are at high risk for the occurrence of relative energy deficiency syndrome (RED-S) [22], including a decrease in bone mineral density and endocrine dysfunction, and reduced musculoskeletal function [23]. Previous literature has emphasized that vegans consume less energy and macro- and micronutrients than omnivores [3]. Whether vegan diets provide sufficient energy availability and preserve bone mineral density is a particular concern for vegan athletes, especially in ultra-endurance races.

Studies investigating the interaction between the gut microbiome and exercise performance in athletes have gradually increased over the past decades by searching the primary role of the gut microbiome on energy metabolism, immunomodulation, inflammatory response, and oxidative stress regulation [24]. Prior investigations have reported that exercise alone may contribute to alterations in the gut microbiome composition [25,26]. However, little is known about the interactions of microbial communities with exercise-related metabolic systems and communication pathways for exercise-related modification. Scheiman et al. [27] emphasized that microbiome modulation by detecting its performance-facilitating organism may be a critical exercise performance component. Metagenomic analyses allow direct comparison of the metabolism in the intestinal microbiota with the host's metabolic results and, integration of metabolomics and microbiome analysis could provide us to identify the microbial influence on host metabolism through bioactive metabolites [28–30]. Although a vegan diet appears to be beneficial for the gut microbiome by consuming foods that modulate/ regulate the microbiome [31], further work should focus on the efficacy of a vegan diet on host-microbiome interactions. To our knowledge, no study determines the vegan vs. omnivore diets' effects on gut metagenomics analyzed using a whole-metagenomic approach.

#### **4. Research design**

A controlled before and after study design

#### **5. Selection of participants**

Volunteer ultra-marathoners will be recruited from the websites of the organizers of ultra-marathon events, vegan communities, runner magazines, and online running communities. In order for them to be eligible for the study, participants will need to take part in the Sri-Chinmoy ultra-marathon race in Basel, Switzerland. Potentially eligible participants will be identified by research staff. Ten vegan and ten omnivore participants will be randomly selected to enroll in the study using computer-generated random numbers. Randomization

and allocation will be performed by an independent researcher. The study will take place in Zurich and Basel, Switzerland.

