## **10. Material and Methods**

### **Preliminary Tests**

Following full verbal and written explanation of the study procedures, participants will be asked to sign an informed consent form. After the enrollment of the study, research data will be collected from the participants at four steps (three visits to the laboratory and the race day) throughout the study. At the first visit (seven days before the race), participants will be invited to the exercise metabolism laboratory. Participants will be informed to come to the laboratory in a fasted state. Fecal samples will be collected using fecal sample collection and preservative kit. Anthropometric measurements (body weight, height and fat-free mass) will be collected. An extended research questionnaire will be administered by research staff. Triaxial accelerometry will be attached to the participants' waist, and will be secured with an elastic belt. The device will be worn continuously throughout the entire study period (seven days before and seven days after the race), except during activities that would submerge the accelerometer in water or if removed for legitimate reasons (e.g., discomfort during sleep). Participants will be informed about how to keep detailed food and liquid diary and will be asked to keep dietary data throughout the study period (14 days). At the same time, a detailed activity log (activity, time and duration) will be kept for the participants.

The second visit will be performed within three to seven days before the race to measure maximum oxygen consumption using indirect calorimetry (Viasys Jager Master Screen CPX, PanGas AG, Dagmarsellen, Switzerland). Participants will be advised to follow their normal diet and to avoid strenuous exercise/ sports 24 hours before the VO2max test. Heart rate will be measured continuously by a heart rate monitor (Polar-S-810 heart rate monitor), and respiratory variables will be recorded every 30 s.

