### **13. Originality of the research**

Although the vegan diet has been widely preferable and studies claiming to be adequate for ultra-endurance athletes, there is still no comprehensive investigation of the impact of the vegan diet applied by ultra-endurance athletes. Therefore, we aim to provide an in-depth investigation of vegan diets by analyzing blood and fecal analysis in ultra-endurance athletes adhered to this diet for the long term. In case of vegan diets are found to be beneficial and sufficient, the study a level of evidence against the belief that the vegan diet may be insufficient for athletes and may provide the framework for future studies to assess veganism's effects in athletic populations. Besides, the athletic population consumes meat products 2- and more fold according to the other individuals. If a Vegan diet provides enough energy availability and balance macro- and micronutrients in the body, we can also recommend consuming the diet for the future of planet-saving. On the other hand, if vegan diets are detrimental for either metabolism, including immunologic or oxidative factors or gut-host crosstalk, veganism's adverse effects could be identified to inform athletes to inhibit its detrimental consequences.

By adding the measurements of oxidant/antioxidant- and muscle fatigue-related parameters, we seek to explore the impact of dietary patterns on body hormesis and fatigue levels in ultra-endurance athletes. Dietary intake data will analyze all diet composition, including nutrient and non-nutrient components, the main determinants of antioxidant defense. We may also determine whether the whole dietary pattern or food intake affects hormesis balance and endogenous antioxidant defense in athletes endured under extreme conditions.

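### Random sampling within two existing diet groups is labelled randomization and allocation; it gives no comparability between diets, yet the aims and section 13 plan causal and advisory conclusions

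*Protocol*

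**What the plan says.** Protocol section 5 (Selection of participants) describes one combined recruitment list: "Volunteer ultra-marathoners will be recruited from the websites of the organizers of ultra-marathon events, vegan communities, runner magazines, and online running communities". From the eligible volunteers, "Ten vegan and ten omnivore participants will be randomly selected to enroll in the study using computer-generated random numbers". The next sentence names the step randomization and continues: "and allocation will be performed by an independent researcher".

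Other sections show that diet precedes enrolment and is not assigned:

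- Section 4 gives the design as "A controlled before and after study design".
- Section 13 describes the work as done "by analyzing blood and fecal analysis in ultra-endurance athletes adhered to this diet for the long term".
- Section 10 (Preliminary Tests), on preparation for the VO2max test: "Participants will be advised to follow their normal diet".

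The conclusions are framed causally. The first aim in section 2 is "To investigate the effects of long-term vegan and omnivorous diet on gut metagenomics in ultra-marathoners". Section 13 says: "If a Vegan diet provides enough energy availability and balance macro- and micronutrients in the body, we can also recommend consuming the diet". It adds that, if results are unfavourable, adverse effects of veganism could be identified so that athletes can be informed.

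**The concern.** A reader who meets the words randomization and allocation expects that chance decided who ate which diet, and that the groups therefore differ only by chance at baseline. Here chance decides only which volunteers on each diet are enrolled. Each sample of ten reproduces the make-up of its own volunteer pool. If vegan and omnivorous volunteers differ in sex mix or training volume, that difference stays in the comparison.

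This bears on the primary outcome. Section 3 of the protocol itself reports that exercise alone may change the composition of the gut microbiome, so training volume is a plausible confounder by the protocol's own account. What is at stake is whether a difference in microbiome or biomarkers may be read as an effect of diet, and whether section 13 can rest advice to athletes on it.

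**Working it through.** **Step 1: what the random numbers decide.** Section 5 applies them to selection into the study within each diet. Sections 2 and 13 describe the diets as long-term, section 10 leaves participants on their usual diet before the VO2max test, and no section assigns a diet. The step is therefore sampling, not allocation.

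**Step 2: what comparability the design does provide.** Sections 5 to 7 require the same named race, age 18 to 49, no history of illness, and no probiotics or antibiotics in the preceding 3 months, identically for both diets. Nothing in selection balances sex or training volume.

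**Step 3: what the before-after contrast removes.** Let a participant's pre-race value be L and the post-race value L + R, where R is the response to the race. The change is R, so a stable additive difference in L between the diets cancels. Two things remain:

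- Aim 1 concerns long-term diet and the microbiome itself, that is L, where nothing cancels.
- If R depends on a confounder C, say R = r + gC, and the pools differ by D in C, the two diets differ in mean change by gD even when diet does nothing.

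**Step 4: illustration of size.** The plan's only figure here is 10 + 10 = 20 participants, and the point does not turn on it. The other inputs are assumptions, not taken from the protocol:

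- a confounder differing by D = 0, 0.5 or 1.0 SD between the pools;
- its correlation with the outcome, rho = 0.3, 0.5 or 0.7;
- a true diet effect of zero;
- a two-sided t-test at 0.05 on one continuous outcome with within-group SD 1. This stands in for the planned microbiome analyses and does not reproduce them.

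The spurious difference is rho × D. Its standard error is sqrt(2/10) = 0.447, so the standardised shift is rho × D / 0.447. That runs from 0.15/0.447 = 0.34 to 0.70/0.447 = 1.57. False-positive rates come from 40,000 simulated studies per setting:

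| D (SD) | rho | Spurious difference (SD) | False-positive rate, sampling within diets | False-positive rate, true random allocation |
|---|---|---|---|---|
| 0 | 0.3 to 0.7 | 0 | 4.9% to 5.1% | 4.9% to 5.0% |
| 0.5 | 0.3 | 0.15 | 6.2% | 5.0% |
| 0.5 | 0.5 | 0.25 | 8.2% | 4.9% |
| 0.5 | 0.7 | 0.35 | 11.4% | 5.2% |
| 1.0 | 0.3 | 0.30 | 9.8% | 4.9% |
| 1.0 | 0.5 | 0.50 | 18.4% | 5.1% |
| 1.0 | 0.7 | 0.70 | 31.7% | 5.2% |

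Under sampling within diets, the mean confounder gap in the enrolled groups was 0.50 SD at D = 0.5 and 1.00 SD at D = 1.0: the whole pool difference. Under true allocation it was zero to within simulation error.

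**The case against.** The strongest reply is that the defect is mostly one of wording. Section 4 does not call the study a randomised trial. Random selection by an independent researcher has a real use: it stops staff hand-picking within a pool, provided more than ten eligible volunteers exist per diet. Both groups are restricted identically on race, age, illness and recent probiotics or antibiotics. The pre/post samples cancel stable level differences. Training history, VO2max, accelerometry and body composition are recorded, and adjustment could be specified in a SAP that was not available for this review. Section 13 is an originality statement, and its conclusions are conditional.

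All of this stands, and it limits the point. It does not make the step an allocation, does not protect Aim 1, and does not remove confounding of the response to the race. Matching at selection cannot be added by a SAP once participants are enrolled.

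A reader might infer more than the documents support:

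- *That vegans and omnivores come through different recruitment channels.* Section 5 gives one combined list. Different channels are possible but not stated.
- *That race exposure is uncontrolled.* Every participant must enter the same named race, and the protocol describes no differing durations.
- *That runners harmed by the vegan diet have already dropped out of view.* The health and racing criteria apply to both diets, and the protocol has no information on such losses.
- *That chance imbalance at 10 versus 10 measures the problem.* A truly randomised study of 20 would have the same chance imbalance. It reflects small numbers, not the absence of allocation.
- *That energy availability should count as enough once the vegan mean is shown to exceed 30 kcal/kg.* The Energy Availability part of section 10.1 gives about 45 as recommended and below 30 as low, so such a rule would equate not low with enough. Adequacy is also mainly a question within the vegan group, separate from randomisation.

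**Conclusion.** The point holds in this form: section 5 mislabels sampling within pre-existing diet groups as randomization and allocation, the step gives no comparability between diets, and sections 2 and 13 frame the results more causally than the design allows. That diet was self-chosen is inferred from its being long-term and unassigned. The conclusion needs only that the study does not assign it.

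The size depends on how far the two pools really differ, which the protocol does not tell us. If they do not differ, the error rate stays at 5%. Over the assumed range of 0.5 to 1.0 SD, with correlations of 0.3 to 0.7, the spurious difference is 0.15 to 0.70 SD and the false-positive rate about 6% to 32%. These figures illustrate the mechanism and do not estimate the bias in this study. The remaining gap in selection is sex and training volume. The correction is cheap and changes what the study may conclude, so it should be made.

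**What to change.** 1. In section 5, delete the reference to randomization and allocation. State that an independent researcher selects participants within two non-randomised diet cohorts. Cost: wording only.
2. In sections 2 and 13, limit aims and conclusions to associations among healthy, competing ultra-marathoners, without recommending or warning against the diet on causal grounds. Cost: wording only.
3. Where volunteer numbers allow, select omnivores to match the enrolled vegans on sex and, as closely as possible, age and training hours. Use random numbers to choose among equally good matches, which keeps the protection against hand-picking. Weekly training hours are already in the planned questionnaire (section 10.1), but it is given at the first visit, after enrolment, so these items would have to be asked at screening. Cost: earlier timing of a few items and a surplus of omnivore volunteers. Random selection already presupposes more than ten eligible per diet, but matching may need more than that.

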## **6. Inclusion Criteria**

- 1) ultra-marathoners aged between 18 to 49 years
- 2) competing in the Sri-Chinmoy ultra-marathon race
- 3) no use of probiotics and antibiotics in the preceding 3 months
- 4) no history of acute or chronic illnesses.

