## **7. Exclusion Criteria**

- 1) ultra-marathoners aged < 18 or > 49 years
- 2) not competing in the Sri-Chinmoy ultra-marathon race
- 3) use of probiotics and antibiotics in the preceding 3 months
- 4) history of acute or chronic illnesses.

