### **Body Composition Assessment**

To assess body composition of participants, they will be asked to visit the research laboratory in a fasted state (after an overnightfast) and refrain from caffeine (at least four hours), alcohol (at least two hours), cigarette (at least two hours), and not to exercise at high intensity for 24 hours before the visit.

Body weight and fat-free mass will be measured using a commercial scale Beurer BF 15 (Beurer GmbH, Ulm, Germany) with 0.1 kg accuracy. Height will be measured while participants are standing, head positioned in Frankfurt horizontal plane, using a portable stadiometer (Seca 213, Hamburg, Germany). Bone mineral density and body fat percentage will be measured using dual-energy X-ray absorptiometry (DXA).

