### **Maximum Oxygen Consumption measurement**

The maximum oxygen consumption (VO2max) will be measured using indirect calorimetry (Viasys Jager Master Screen CPX, PanGas AG, Dagmarsellen, Switzerland) by the method used in a previous study on male runners by Shing et. al [42]. The method includes an incremental running test performed on treadmill. The test protocol will start at 10 km h, 0% gradient with the speed increasing by 1 km h each minute until a speed of 18 km h. After 1 min at 18 km h, the treadmill gradient will be increased by 1% each minute until volitional fatigue. Heart rate will be continuously measured Polar-S-810 heart rate monitor respiratory variables will be recorded every 30 s. Perceived exertion will be evaluated using Borg Scale 6 to 20 [43]. Higher score indicates higher exhaustion.

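### Ten runners per diet are drawn without regard to sex although both sexes are eligible, so the sex mix can differ between diets and confound the Aim 3 and 4 comparisons

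*Protocol*

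**What the plan says.** Section 4 describes the study as "A controlled before and after study design". The two groups are defined by the diet that runners already follow. Section 5 fixes how they are filled: "Ten vegan and ten omnivore participants will be randomly selected to enroll in the study using computer-generated random numbers". It mentions no stratification, quota or matching on any characteristic.

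Among personal characteristics, section 6 restricts age ("ultra-marathoners aged between 18 to 49 years") and illness history, and section 7 mirrors this ("ultra-marathoners aged < 18 or > 49 years"). The other criteria concern race entry and use of probiotics or antibiotics. Sex appears in neither list. In the planned methods it appears once, where the VO2max test is to be run "by the method used in a previous study on male runners".

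The comparisons concerned are in section 2. Aim 3 covers energy availability and nutrient intake and is to "compare the differences between vegan and omnivorous ultra-marathoners". Aim 4 is "To explore the effects of long-term vegan and omnivorous diets on exercise capacity, oxidant/antioxidant capacity, and muscle fatigue in ultra-marathoners". Section 10.1 adds fat-free mass, body fat and bone mineral density.

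**The concern.** VO2max and body composition can be expected to differ between men and women. If one diet group holds more women than the other, part of that sex difference appears in the diet contrast.

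There are two routes. One is chance: with ten per group, simple draws from identical pools can produce unequal counts. The other is systematic: recruitment runs partly through vegan communities and partly through running channels, and the two volunteer pools need not have the same share of women. A random draw within each diet reproduces such a difference, because it samples from the pools and does not assign diet.

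This is a matter for the protocol. Once the twenty runners are enrolled, an analysis can adjust for sex but cannot restore the balance.

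**Working it through.** **Inputs from the protocol.** Ten runners per diet, a simple draw, no sex criterion. The protocol states no power, SD or effect size, so there is no figure of its own to reproduce.

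**Assumptions, shown as ranges.** Share of women p among volunteers; number of volunteers per diet; sex gap g in within-sex SD units (1 to 1.5); two-sided 0.05 t-test without a sex term.

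**Step 1: chance imbalance, very large equal pools.** Let A and B be the counts of women, each Binomial(10, p). For p = 0.5, A − B + 10 is Binomial(20, 0.5), so:
- P(equal) = 184,756 / 1,048,576 = 0.176
- P(differ by 1) = 2 × 167,960 / 1,048,576 = 0.320
- P(differ by 2) = 2 × 125,970 / 1,048,576 = 0.240
- P(differ by 2 or more) = 1 − 0.176 − 0.320 = 0.50
- P(differ by 3 or more) = 0.503 − 0.240 = 0.26

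Summing the product of the two binomials in the same way for other shares:

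| Share of women | Differ by 2 or more | Differ by 3 or more |
|---|---|---|
| 10% | 24% | 6% |
| 20% | 39% | 16% |
| 30% | 46% | 22% |
| 50% | 50% | 26% |
| 30% v 50% | 65% | 43% |

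**Step 2: finite equal pools.** Drawing ten from N volunteers of whom F are women makes each count hypergeometric:

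| Pool per diet (women) | Differ by 2 or more | Differ by 3 or more |
|---|---|---|
| 12 (4 to 6) | 8-10% | 0% |
| 15 (4) | 20% | not computed |
| 15 (5) | 22% | 4% |
| 20 (6) | 31% | 9% |
| 20 (10) | 35% | 12% |
| 30 (9) | 37% | 14% |
| 30 (15) | 42% | 17% |

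The smaller the pool, the closer the draw is to taking everyone, and the less chance has to do with the result.

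**Step 3: shift in the diet contrast.** A difference of k women out of ten shifts the contrast by (k/10) × g. For k = 3: 0.3 × 1 = 0.30 SD and 0.3 × 1.5 = 0.45 SD. For pools of 30% and 50% women the expected shift is (0.5 − 0.3) × g = 0.20 to 0.30 SD, and it does not average out over draws.

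**Step 4: false positives without a sex term, no diet effect.** Simulation of 10 v 10:
- Equal pools, 30-50% women, over all draws: about 5% for both gaps.
- Given a difference of exactly three women: about 6.5-7.6% in most settings. The top corner (30% women, gap 1.5 SD) came out slightly above 8%.
- Given a difference of none or one: about 2-3%, so the test is conservative.
- Pools of 30% v 50% women, over all draws: about 7% (gap 1) and 8% (gap 1.5).

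**The case against.** The strongest counter-case has four parts.

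**Chance imbalance from equal pools is not bias.** A reader might infer from the 0.30-0.45 SD shift that the false-positive rate climbs to 9-12%, by putting that shift into a noncentral t with a single SD. That does not follow. Once the sex counts are fixed, only within-sex variation is left in the numerator, while the unadjusted residual SD still contains sex. Averaged over all draws from equal pools the error is nominal. This part stands.

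**The very-large-pool probabilities are upper-end.** Volunteers must be entrants of one named race aged 18 to 49, then split by diet, so pools may be small. If barely ten vegans volunteer, there is no vegan draw. This stands, and the finite-pool figures are the more relevant ones. Small pools do not remove the second route, a different sex mix among the volunteers themselves.

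**Adjustment could do much of the work.** A sex term may be in an analysis plan that is not shown, and its absence from the protocol is no finding. With sex modelled and 3 v 6 women, the variance of the diet contrast is 1.10 times the balanced value. The 95% half-width is then 2.11 × √(0.2 × 1.10) = 0.99 SD, against 2.11 × √0.2 = 0.94 SD when balanced. So if sex is modelled, balanced selection adds only about 5% in precision at that imbalance. Conversely, balanced selection alone removes the shift but leaves sex in the residual SD of a plain t-test.

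**The main outcomes are less exposed.** The primary outcome compares stool before and after the race in the same runner, and energy availability is already divided by fat-free mass. Both points stand. A reader should not infer that the primary analysis is confounded in the same way.

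A reader might also take the reference to male runners as a sign that only men will be enrolled. That phrase describes where the treadmill method comes from; the eligibility lists do not restrict sex.

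**Conclusion.** The point holds as a modest weakness of the selection rule. Sex is open, the draw ignores it, and diet is self-chosen, so nothing in the protocol keeps the sex mix alike in two groups of ten. The VO2max and body-composition comparisons are exposed, and energy availability in part.

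The size depends on three unknowns: the number of volunteers, the share of women and the sex gap. With 30-50% women and pools of 15 to 30 per diet, a difference of two or more women is plausible (about one draw in five to two in five). With pools of 12, or with few women, it is less likely, and if nearly all volunteers are of one sex the issue fades. The more serious case is unequal pools, where the shift is systematic and the unadjusted error reaches about 7-8% under the assumed 30% and 50% shares. The documents do not show that the pools differ in this way; they only leave it possible. Sex is also not the only characteristic on which the diets could differ, so balancing it removes one confounder and not all of them.

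**What to change.** Change section 5 before any runner is selected: select the ten vegans first (at random if more than ten are eligible), then draw the ten omnivores at random within sex, to the same numbers of men and women as far as the omnivore pool allows. If exact matching fails, state the counts reached.

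The cost is one sentence and recording sex before the draw. The downside is a narrower omnivore pool in each draw, and exact matching may be impossible if few volunteer. How sex enters the analysis can be left to the statistical analysis plan.
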